#### Qualitative Data Analyses

Concerning qualitative data from the semistructured interviews (intervention and control groups), they have been analyzed through content analysis: we have identified patterns across collected texts which are coded according to key elements. These can include, for instance, reported advantages and drawbacks of the game, or players’ opinions on the usefulness of the game in general. The semistructured interviews are either video or audio recorded depending on the availability of the participants, during the lunch break or in the late evening after the classes. In-depth analyses were conducted using a reflexive approach so as to appraise and evaluate how subjectivity and context influence the research processes, especially during the interpretation of the data on intimate topics like mental health. Before the association with the quantitative data, the texts will be cross-analyzed to identify similarities and differences between the experience with either the escape game or the email.

Data from the debrief at the end of the game were recorded automatically within the game. The texts were collated in a single document which was used to generate repeated and automated messages. Through artificial intelligence and, more specifically, the machine-assisted topic analysis (MATA), the human conversation will be processed to simulate answers to players’ requests. The outcome will correspond to a chatbot, which will a computer program that will be able to animate a discussion and provide tips concerning mental health–related issues.

### Ethical Considerations

The study has received the French identifying number (ID-RCB) 2024-A00436-41 from the National Agency for the Safety of Medicines and Health Products. This number is compulsory for registering projects on human subjects in France.

The Ethics and Health Research Center of the University of Bordeaux approved the study (2024-A00436-41). The procedures are in accordance with the Helsinki Declaration of 1975, as revised in 2024.

It is compulsory that students carefully read the consent form and sign it electronically (by clicking on the “I agree button”) in order to participate to all steps of the study and share their data collected through questionnaires, interviews, and during the game. The consent form includes all the details of the study: (1) principal investigator, (2) rationale, (3) objectives, (4) methods, (5) length, (6) conditions of the storage data and analyses, and (7) expected impact. Students access directly to the consent form when they click on the link in the social media posts and the study invitation email. Participants are given the chance to opt out.

All confidential information, including participants’ contact details or other sensitive data like self-reported mental health status will only be accessible to authorized staff members from the study. Thus, information is quasi-anonymous for the proper running of the study. In fact, the email address is necessary to organize the game sessions, to send the links to the web-based questionnaires and to schedule the internet-based interview. The phone number is also required to resolicit the participants, only once, for the organization of the game session. We guarantee the noncommercial use of the email addresses and the phone numbers.

Overall, participants are informed that they are not blinded.

All data, including the sensitive ones, are imported automatically from the software Sphinx to Excel. The document is protected by a password known only to the principal investigator and the statistician of the research team. The data will be destroyed 2 years after the last article based on this study is published. The collection, storage, and analysis of the data comply with the European General Data Protection Regulation (GDPR).

As already mentioned, students will receive US $21.5 gift cards for their participation to the study. The authors have filled the CONSORT-EHEALTH (Consolidated Standards of Reporting Trials of Electronic and Mobile Health Applications and Online Telehealth) form V1.6.1 (Multimedia Appendix 3).

## Results

### Key Dates of the Study

The study received funding by the French National Research Agency in January 2022. The production of the EscapeCovid Game ended in March 2023. The cocreation process, the test, and the refinement of the intervention lasted 15 months. For the evaluation of the finalized game, the collection and analyses of qualitative data through semistructured interviews has been completed by September 2023. The end of the evaluation phase through the RCT is scheduled to be completed by the end of June 2025. The results of the mixed methods analyses are expected to be published by the end of December 2025. The timeline of the study is illustrated in Figure 1.

**Figure 1 figure1:**
[figure not shown]
Timeline of the phases of the study.

### Study Population

The recruitment started in December 2023.

As of November 4, 2024, a total of 191 students have answered the baseline questionnaire and have been randomly assigned to one of the 2 arms, 90 intervention versus 101 control. A total of 23 students have played the EscapeCovid Game (intervention arm) and 53 are in the control arm. Specifically, 54% (103/191) of the participants at the baseline are students in health care disciplines; 11.5% (22/191) in sciences and technologies; and the remaining participants study other subjects 34.5% (66/191) including psychology, law, and so on.

Concerning qualitative data, 20 students (10 for each arm) have been interviewed on the appreciation, relevance, and acceptability of either the game or the email. Students of the game arm were between 18 and 28 years of age. There were 9 females and 1 male. Their year of study ranged from the first year of their bachelor’s degree to the first year of their doctoral studies. Fields of study included medicine, chemistry, physics, biology, sociology, speech therapy, and political science. Students of the control arm were between 18 years and 28 years old. Their year of study ranged from the second year of their Bachelor’s to the third year of their doctoral studies. Fields of study included medicine, physics, nursing and marketing.

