#### The Randomized Controlled Trial

We implement a rigorous RCT design using pre- and postintervention data coming from online self-administered questionnaires. The sample must be of at least 500 students at the University of Bordeaux. We estimated a sample size of 500 participants for the 2 arms: statistical power=.80, Cronbach α=.05, Cohen *d*=0.5, and 40% attrition with a 2:1 allocation ratio for the intervention group.

At study entry, the 500 students complete the online baseline questionnaire. Among them, 250 students play the EscapeCovid Game while 250 students receive an email with tips and resources for managing their stress during the COVID-19 pandemic. Participants are randomized so that the 2 groups are similar in terms of sex, age, and field of study (stratified balanced randomization). Participants are informed from the beginning of the study that they can be allocated to either the intervention of interest or the comparator. We tell students in the control arm that they are in a waiting list and that they can play the game once the experiment is concluded.

Inclusion is stopped when at least 500 participants have completed at least 3 quarters of each questionnaire, and 250 have played the game until the end. The statistician and the project manager of the EscapeCovid study are in charge of generating the random allocation sequence, enrolling participants, and assign them to one of the 2 arms.

Briefly, the 250 students of the intervention arm (1) complete the online baseline questionnaire, (2) play the EscapeCovid Game at their home within the week after the online baseline questionnaire—a link to the game is given at the end of the questionnaire, and (3) complete the same online questionnaire of the baseline plus some items on the appreciation of the game (satisfaction survey) 2 days after having played the game. After some tests with Tricky staff, the game duration is estimated at about 2 hours, from the online registration with the creation of an account, until the end of the debrief. Instructions to connect and play online are provided in an email sent by the start-up to the student of the intervention arm 2 days before the game session.

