#### Quantitative Data Analyses

For the data from the RCT, we will compare the answers between exposed and nonexposed students (intergroup) and measure the change in their answers within the intervention group before and after playing the game and debriefing (intragroup). Our primary analysis will be based on intention-to-treat at the individual level using linear regression comparing the outcomes of the intervention and the control arm. We will measure our primary outcomes in terms of absolute scores and as a percentage of the total possible score. We will control baseline covariates: (1) gender, (2) age, (3) field of study, (4) year of study, and (5) self-perceived health. We will analyze the data from all participants only if at least 3 quarters of the questions are completed. We consider that some users will not go through all questionnaire pages. Missing values will be imputed by replacing them with the mean or median values of the dataset at large, or some similar summary statistics.

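### The game-arm post-test is timed from playing, so non-players have no post-test date and the analysed set depends on playing, despite the intention-to-treat label; the interim counts show this could matter

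*Protocol article*

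**What the plan says.** All references are to the protocol article.

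- **Planned loss** (The Randomized Controlled Trial). The sample size rests on "40% attrition with a 2:1 allocation ratio for the intervention group". This is one figure for the trial, not one per arm.
- **Schedule** (same section). The game is to be played within a week of baseline, and the game arm's second questionnaire falls "2 days after having played the game". Controls get their email on the day of baseline and their second questionnaire 2 days later.
- **Stopping inclusion** (same section). Inclusion ends when at least 500 participants have filled in three quarters or more of each questionnaire and 250 have finished the game.
- **Reminders and replacement** (Recruitment of Study Population). Up to five reminders for the second questionnaire go to all 500 participants, and up to five more go to the game arm about booking and playing. If a student still does not reply, new students are invited.
- **Analysis** (Quantitative Data Analyses). "Our primary analysis will be based on intention-to-treat at the individual level using linear regression", but only participants with at least three quarters of the questions completed are analysed.
- **Progress at 4 November 2024** (Study Population). 191 students "have been randomly assigned to one of the 2 arms, 90 intervention versus 101 control". Then: "A total of 23 students have played the EscapeCovid Game (intervention arm) and 53 are in the control arm". Recruitment began in December 2023, and completion is expected by the end of June 2025.

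**The concern.** An intention-to-treat comparison needs an outcome, or at least a planned outcome assessment, for every randomised student whether or not the intervention was taken up. Here the assessment date in one arm exists only if the student plays. A control needs only to be sent an email to have a date. A game-arm student must book a session, have a suitable computer and spend about 2 hours.

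If few game-arm students play, and those who do are more motivated or less distressed, the game arm that is analysed is a self-selected part of the randomised arm, set against a less selected control group. Any difference then mixes the effect of the game with the effect of who stayed. Recruiting more students to reach 250 players enlarges the selected group without undoing the selection. The interim counts matter because they show how large the non-playing group could be.

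**Working it through.** **1. The plan's own figure.** Inputs: power 0.80, alpha 0.05 (taken as two-sided), d = 0.5, 40% loss. The calculation gives 126 completers at 1:1 and 144 at 2:1. Dividing by 0.60 gives 210 and 240. The stated 500 is not reproduced. That is a separate matter, but it means that power is not the issue here (step 5).

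**2. The interim counts.** Exact binomial 95% intervals:

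| | Not counted as progressed | Proportion | 95% CI |
|---|---|---|---|
| Game (not played) | 90 − 23 = 67 of 90 | 74% | 64 to 83 |
| Control (not among the 53) | 101 − 53 = 48 of 101 | 48% | 37 to 58 |
| Overall | 115 of 191 | 60% | 53 to 67 |

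Fisher's exact test between arms gives p = 0.0002. The game and overall intervals lie above 40%; the control interval includes it.

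**3. Could students still in process explain this?** For the game arm to end at 40%, 36 of 90 may be lost (0.40 × 90), so 67 − 36 = 31 students would have to be pending and all go on to play. If intake was even over about 11 months (an assumption, since no accrual curve is given), the game arm gained 90/11 ≈ 8 a month. Then 31 is nearly four months' intake, on a schedule of about a week. Setting aside one month's intake (191/11 ≈ 17):

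- split between the arms: 59/82 = 72% against 40/93 = 43%;
- all 17 taken from the game arm: 50/73 = 68% against 48%, p = 0.008.

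**4. The rules side by side for a student randomised to the game who never plays.**

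- Second questionnaire: dated from playing, so no date exists. Reminders go to everyone, but they set no date either.
- Stopping rule: the student does not count towards the 250. At 23/90, reaching 250 players would take 250 ÷ (23/90) ≈ 979 students randomised to the game, against 250 planned.
- Non-response: new students are invited.
- Analysis: without a sufficiently complete questionnaire, the student is left out.

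Each rule alone might be tolerable. Together they make entry to the analysis depend on playing in the game arm, with no counterpart among controls.

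**5. Power.** Purely as a stress test, apply the snapshot rates to 250 per arm: 250 × 23/90 ≈ 64 and 250 × 53/101 ≈ 131. Power at d = 0.5 is about 90%. At 60.2% loss the required enrolment is 126/0.398 ≈ 317 or 144/0.398 ≈ 362, both below 500.

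**6. Illustration of bias (assumed, not estimated).** Suppose that the students retained are the top 25.6% (23/90) and top 52.5% (53/101) on a standard normal trait that has correlation r with the outcome. The trait means are 1.258 and 0.759, a difference of 0.499. The shift in the treatment difference is r × 0.499: 0.05, 0.15 and 0.20 SD for r = 0.1, 0.3 and 0.4. The largest is 0.20/0.5 = 40% of the planned effect. The documents do not supply r, and covariate adjustment could reduce the shift.

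**The case against.** The strongest reply is that the Study Population counts are not attrition. They are a dated snapshot of an open trial. Having played is receipt of the intervention, not completion of the outcome, and the stage reached by the 53 controls is not defined. No second-questionnaire counts are given. Game sessions must be scheduled, can be played in groups of 4 with a guide, and come after up to five booking reminders, so delay should be longer in the game arm. Invitations go out in batches, so even accrual may not hold. All of this stands.

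A reader might therefore infer from 74% against 48% that the planned 40% has been shown to be wrong, that the arms are already differentially selected, or that only about 64 and 131 students will be evaluable. The documents support none of these. The two percentages may measure different things, no comparison has yet been made, and the stopping and replacement rules mean that inclusion would not end at 64 and 131. Nor is sample size harmed at d = 0.5.

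It can also be said that second-questionnaire reminders go to all participants and that the analysis is declared intention-to-treat, so non-players may in practice be followed up. That may be the intention. As written, however, the reminders carry no date for non-players, and the one date given for the game arm requires play. The article also acknowledges that recruitment and retention are difficult, but this does not resolve the conflict.

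**Conclusion.** The point holds as a conflict between stated rules. Timing the post-test from playing, stopping inclusion on players and completers, inviting new students after non-response and restricting the analysis to sufficiently complete questionnaires together make the game-arm analysis set depend on playing. This is at odds with the declared intention-to-treat analysis.

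The counts are a warning about scale: 67 of 90 game-arm students had not played at the snapshot and, on the text as it stands, had no post-test date. Overall 60% had not progressed, against a planned 40%. This reading counts every student who had not progressed as not yet retained and takes the 53 as controls who had gone through the control steps. Explaining the game-arm figure by pending students alone would need 31 of the 67 still to play, which is unlikely on the stated schedule but not excluded.

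The threat is bias, not power. Its size is unknown; 0.05 to 0.20 SD is an illustration on assumed correlations. The change should be made while recruitment is open, because post-tests not collected on time cannot be recovered later.

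**What to change.** 1. Send the second questionnaire to every randomised student in both arms on the same fixed day after randomisation, late enough to cover the one-week game window, whether or not the student played. Attach the existing reminders to that date.
2. Analyse all of them in the arm to which they were randomised. Do not count later invitees as substitutes for randomised students who did not reply; those students stay in the denominator. Reconcile the stopping rule with this.
3. Define the stage reached by the 53 controls, and report second-questionnaire completion by arm.
4. Restate the 40% from those completion counts, by arm, and not from the number who played.

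The cost is some rewording, one change to the emailing schedule and one extra tabulation. The downside is that, for some students, the post-test will no longer fall exactly 2 days after the game or the email. The restated attrition may also look less favourable than 40%.

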### Preliminary Quantitative and Qualitative Results

As of November 4, 2024, the sample size of the trial is too small for providing robust data and for reaching significance level.

As far as qualitative data are concerned, we completed all 20 interviews. According to the students from the intervention harm, the game was appealing and fun. The use of gamification to communicate mental health-related messages was appreciated.

I like the initiative of doing something more fun, more educational than just distributing information, which is also a way in itself, we agree, but I like the way of trying to learn.Student 7–Male

The game was described as “innovative,” “unique,” “instructive,” and “beneficial” considering its alternative approach to conventional public health interventions, for example, educational materials, and social marketing campaigns.

The notion of stigmatization emerged. Attached outcome was the appraisal and change of beliefs about mental health.

I found it very interesting that we raise awareness about mental health because I have the impression that it is something that we talk about more than before but there is still a taboo behind it.Student 2–Female

The game also contributed to increase participants’ mental health literacy.

It gave me knowledge I didnot have about mental health.Student 1–Male

The impact of the intervention on support recognition and management of emotions was also positive.

The way in which the symptoms or rather really what the person thinks to themselves are well represented and so it really allows us to understand what is going on in the person's head and also to know the symptoms and emotions. So it's very interesting, rather than just listening to someone talk about it and having a slide, it's much better.Student 9-Female

The other study outcome (teach positive coping strategies) was also reported:

Well, you see that I have to do things that finally make us happy and otherwise, not to work too late, to take a break to eat, to see my friends and that's it and from time to time go out when we need to get some fresh air.Student 5-Male

However, the students also declared that the content of the game should be enriched with the presentation of more coping strategies in order to support the player’s psychological well-being. Thus, the impact of the intervention should be directly on the mental health of the players and not only on their knowledge and beliefs.

Not particularly, I don’t think so, it was more focused on knowing emotions rather than how to manage them.Student 1-Male

In comparison to the game, the informative email was not an immersive experience and was not expected to influence students’ cognition, affect, potential, and health behavior. However, it provided useful tips to students from the control arm, including the following: a list of existing sources in case of mental health distress (eg, helplines and free-of-charge consultations with a psychology based at the University of Bordeaux); breathing techniques and meditation; and mental health problems explained with accessible but accurate terminology.

It gave me knowledge I didn't have, about the numbers to contact in case of need [...] we can't know them all by heart and I think that having them all written down in an email or in a document, well I think that it can help us because not everyone knows where to refer and where to go in case of need.Student 1-Male

The usefulness of the email consisted in the fact that it could be used as a memorandum and repertoire of the basics of mental health literacy: knowing that mental health includes both positive mental health and the absence of a mental health problem; knowing the signs of the most common mental health problems (depression, anxiety, and stress); recognizing and managing emotions; learning coping strategies; and having a list of the most known services in case of a mental health distress.

As of November 4, 2024, data from the game debriefs is not transcribed and cannot be analyzed.

## Discussion

### Principal Findings

This paper outlines the protocol for the evaluation of a cocreated Escape Game on students’ mental health outcomes contributing to prevent and manage mental health diseases and promoting psychological well-being: mental health literacy, appraisal and change of beliefs about mental health, management of emotions, and development of coping strategies. The evaluation is conducted through mixed methods, combining the quantitative results of a RCT with the qualitative results of semistructured interviews.

Concerning quantitative, as of November 4, 2024, the recruited sample is too small to make inferences on the impact of the game. Actually, recruiting students is the hardest challenge of the trial. All along the study, we have observed that the most successful recruitment strategies are: offering gift cards to students completing the whole study (baseline questionnaire, intervention or control arm, and repeated questionnaire); counting on the support of student associations promoting the study among members; and involving professors who present the study during their classes. We will reinforce these strategies to attract and retain students in the trial.

As for the qualitative data, the recruitment of students was far easier and we rapidly interviewed 20 participants by September 2023. The comparison of the responses across the 2 groups, game versus email, showed that gamification improved the retention of messages, especially in terms of recognition and management of emotions. On the other hand, email was considered useful as a memorandum of mental health–related information. In particular, students appreciated the list of available services that they could keep and save for contacting professionals in case of need.

Based on preliminary results, these 2 distinct tools, the EscapeCovid Game, and the informative email, could prove to be mutually complementary in promoting student mental health. By consolidating the specific advantages of each approach while mitigating their respective limitations, we can aspire to a more holistic and informed approach to strengthening psychological well-being within the student community.

